### Intervention

Patients in the intervention group will receive access to a Web-based recovery program, ICUTogether that is accessible via smart devices and personal computers. The mobile website will provide information about health and well-being during recovery, including advice about exercise, sleep, and nutrition. Information will be provided on the recovery process, the signs and symptoms of potential complications during recovery, and when and how participants should seek professional help. Participants will be encouraged to keep a journal to promote reflection on progress over time and to explore their thoughts and feelings during their recovery. A chat room will also be available and participants will be able to post items to share with other participants in the study.

Participants will be given access to the mobile website 2 weeks following discharge from the hospital. A hard copy the self-help guide and telephone call will guide participants regarding the use of the site. If the participant is still unable to use the website, a researcher will visit their home and provide direct support with it. A demonstration of the functionality of the mobile website by a researcher will also be given at that time. The frequency of use of the website is at the discretion of the participants who will be encouraged to use the site as frequently as they wish. Each time a participant logs in, they will be prompted to complete a symptom checker that will identify material most useful to the participant at that point in time. The score from the symptom checker will be monitored and an alert notification will be sent to the researchers when the scores reach a certain level and thus gives cause for concern. Participants will receive a weekly email summarizing their participation over the previous 7 days and indicating any days they have not participated along with a prompt to continue participating.

The mobile website was developed by an external provider in collaboration with the researchers. The mobile website is being tested for ease of use and navigation properties by the researchers, clinicians, and a group of ICU survivors prior to commencement of the study.

**Figure 1 figure1:**
[figure not shown]
Study design. ICU: intensive care unit; HADS: Hospital Anxiety and Depression Scale; IES-R: Impact of Event Scale–Revised; EQ-5D-5L: 5-level 5-dimension EuroQoL; MSPSS: Multidimensional Scale of Perceived Social Support.

### Control Group

The comparator, the control group, will receive usual care. Usual care is defined as ongoing management by the participants’ general practitioner (GP). There is no specific after care provision for ICU survivors offered at the study site. At the time of discharge from the hospital, survivors are discharged back to the care of their GP with additional services provided as necessary. These services do not include any specific ICU aftercare provision, for instance, follow-up by the ICU team. There will be no contact with the control group beyond consent and postal surveys.

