### Data Collection and Measures

Following the consent process, demographic data will be collected from the participants’ health records, which will include the age, gender, admission diagnosis, severity of illness (APACHE III), existing comorbidities, and ICU length of stay. Data will be collected from participants at the following 3 time points: 2 weeks post discharge, 6 months post discharge, and 12 months post discharge (primary timepoint). The following three outcome measures will be used in the study: the Hospital Anxiety and Depression Scale (HADS), the Impact of Events Scale Revised, and the 5-level 5-dimension EuroQoL. All 3 measures will be completed at each of the 3 time points. The level of family support will also be collected at these time points via the Multidimensional Scale of Perceived Support [14]. Table 1 provides a brief description of each of the outcome measures. Participants in both groups will receive the 3 surveys by email 2 weeks post discharge from the hospital to complete the first data collection time point. At the following 2 data collection time points, the 3 surveys will be sent by via email to both groups. All participants will also be contacted by telephone to provide a prompt to complete the surveys at the data collection time points.

**Table 1 table1:** Summary of outcome measures and description.

Outcome measure		Number of items	Description

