#### Measurement of Costs and Benefits

Benefits will be measured using 5-dimension EuroQoL. Intervention costs will be measured through discussions with the mobile website developers about the requirements to maintain the website for a 1-year period. A plan for promoting the mobile website to future ICU survivors will be prepared, detailing the elements that will be included. Health care costs will be measured by a patient diary for GP visits, health practitioner visits, and medication use. Linked data will be used to measure emergency department visits, outpatient visits, and hospital usage. Personal and productivity costs will be measured by a patient diary, which will record the number of times health-related services and health promotion resources are accessed, travel details to access these resources, and time spent absent from paid work.

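### The Control Group section allows controls only postal surveys after consent, but Data Collection and Measures emails surveys to both arms and telephones everyone; the two rules cannot both be followed.

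*Protocol article*

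**What the plan says.** Control Group defines usual care as management by the general practitioner, notes that the site has no specific ICU aftercare, and ends: "There will be no contact with the control group beyond consent and postal surveys".

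Data Collection and Measures sets a different procedure. At the first time point, "Participants in both groups will receive the 3 surveys by email 2 weeks post discharge from the hospital". At 6 and 12 months, "the 3 surveys will be sent by via email to both groups". On reminders: "All participants will also be contacted by telephone to provide a prompt to complete the surveys at the data collection time points". The same section names the main time point: "12 months post discharge (primary timepoint".

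Three other sections bear on the point:

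- Intervention gives the intervention arm further contact as part of the program. A hard-copy guide and "telephone call will guide participants regarding the use of the site", and "Participants will receive a weekly email summarizing their participation over the previous 7 days".
- Measurement of Costs and Benefits relies on participant records for some items: "Health care costs will be measured by a patient diary for GP visits, health practitioner visits, and medication use".
- Statistical Analysis plans multiple imputation under a missing-at-random assumption. Its regression covariates include allocation and the baseline outcome measures.

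**The concern.** Two explicit instructions in the current text disagree about how the primary outcome is obtained from half the trial. One specifies post and no further contact; the other specifies email and a telephone prompt. A coordinator cannot comply with both.

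HADS is completed by participants who cannot be blinded to allocation. If controls answered on paper without a prompt while the intervention arm answered by email after a telephone call, two things could go wrong. Answers could differ because of the mode, and the proportion and type of people who reply could differ by arm. Blinding the analyst addresses neither. The 2-week survey comes under the same conflicting rules, so if it serves as the baseline, the baseline covariate is exposed as well.

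The protocol article reports that recruitment is under way, so someone is already choosing between the two instructions.

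**Working it through.** **1. The two sections side by side**

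| Item | Control Group | Data Collection and Measures |
|---|---|---|
| Survey mode for controls | Post | Email, all three time points |
| Telephone prompt for controls | Excluded | Given to all participants |
| Contact for consent | Allowed | Not at issue |

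Three readings are possible:

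- Data Collection and Measures governs both arms: same mode and same prompts.
- Control Group governs controls, and Data Collection and Measures governs the intervention arm: post without prompt against email with prompt.
- Staff vary in which they follow: collection is inconsistent within the control arm.

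Only the first gives uniform collection.

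**2. The plan's own figure**

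Inputs from Sample Size: 2-point HADS difference, effect size 0.44, alpha .05, 80% power, 81 per group.

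- Implied SD = 2 / 0.44 = 4.55; an SD of 4.5 gives 2 / 4.5 = 0.444.
- A two-sided two-sample t test needs 80.44 per group at 0.444, which rounds up to 81. At exactly 0.44 it needs 82.05.

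The stated 81 is therefore reproduced, and the contradiction does not touch it.

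**3. Possible bias under assumed attrition**

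The protocol states no attrition rate for either arm, so every loss rate and gap below is an assumption. Let m_I and m_C be the fractions missing at 12 months in the intervention and control arms. Let g be the non-responder minus responder mean HADS, the same in both arms. The responder mean in each arm lies m × g below that arm's full mean, so

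bias in (intervention − control) = (m_C − m_I) × g.

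| Missing, intervention / control | g = 1 | g = 2 | g = 3 |
|---|---|---|---|
| 10% / 20% | 0.1 | 0.2 | 0.3 |
| 10% / 30% | 0.2 | 0.4 | 0.6 |
| 20% / 40% | 0.2 | 0.4 | 0.6 |
| 20% / 20% | 0 | 0 | 0 |

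With 20% / 35% missing and a gap of 0.5 to 1 SD (2.25 to 4.5 points): 0.15 × 2.25 = 0.34 and 0.15 × 4.5 = 0.68 points.

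The non-zero results run from 0.1 to about 0.7 points, or 5% to 34% of the 2-point target (0.1 / 2 and 0.68 / 2). Taking higher HADS as worse, a benefit appears as a negative difference, so a positive bias shrinks it: a true −2 would be seen as −1.9 to −1.32.

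**4. Power**

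Complete-case t-test power at effect size 0.44 is 0.795 with no loss, 0.702 at 20% / 20% and 0.695 at 10% / 30%. The last two both leave 130 participants (65 + 65 and 73 + 57). Uneven loss therefore costs almost no power beyond the total loss; the specific issue is bias.

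**The case against.** The strongest reply is that Data Collection and Measures is the section dedicated to this subject. It states the common procedure three times: both groups at 2 weeks, both groups at the later time points, and all participants by telephone. Control Group describes usual care, and its closing sentence may have been meant only to say that controls get no supportive contact. This stands to the extent that the documents do not show that collection differs by arm. It does not remove the conflict, because the sentence as worded names post and excludes the telephone prompts.

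Four stronger inferences are tempting, and the documents do not support them:

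- **That differential attrition follows.** It is a risk under one reading. No rates are given.
- **That imputation is no help.** Missingness that depends on allocation and observed scores is missing at random, and an imputation model containing those variables can handle it. What would remain is a mode effect, and non-response driven by the unobserved outcome. The figures above are complete-case figures, not forecasts for the planned analysis.
- **That control-arm costs would be under-recorded.** The protocol does not say how diaries are issued or returned. They could be given at consent or sent with the surveys, both of which the control sentence permits. Emergency, outpatient and hospital use come from linked data and need no participant contact.
- **That the weekly emails and support call are part of the fault.** They are delivery of the intervention and exist whichever section governs.

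**Conclusion.** The contradiction is real, is in the current text, and concerns collection of the primary outcome; it should be corrected. Whether it causes harm depends on which section staff follow. If Data Collection and Measures governs, mode and prompting are equal and no bias arises from this source. If the control sentence is applied to controls alone, a mode effect (not quantified here) and arm-dependent non-response become plausible, and imputation would correct the latter only in part.

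The range of about 0.1 to 0.7 HADS points rests on assumed losses of 10–20% in the intervention arm and 20–40% in the control arm, an assumed non-responder gap of 1 to 4.5 points common to both arms, and a complete-case analysis. It is zero when loss and gap are equal. Its direction, if worse-off controls are the ones lost, is towards hiding a benefit, not creating one.

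**What to change.** Reword the last sentence of Control Group so that it excludes intervention or supportive contact only, and state the common collection procedure there. For example:

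> Controls receive no access to the program and no supportive contact from the study team. They receive the same emailed surveys, the same telephone prompts (number, timing and script) and the same cost diaries as the intervention group. Any paper fallback is offered equally to both groups.

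As recruitment has begun, confirm which procedure has been used for controls so far, and record survey mode and prompts for each participant from now on.

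The cost is a wording change. Data Collection and Measures already plans the emailed surveys and telephone prompts for everyone, and the sample size and other stated figures stay as they are.

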### Data Collection and Measures

Following the consent process, demographic data will be collected from the participants’ health records, which will include the age, gender, admission diagnosis, severity of illness (APACHE III), existing comorbidities, and ICU length of stay. Data will be collected from participants at the following 3 time points: 2 weeks post discharge, 6 months post discharge, and 12 months post discharge (primary timepoint). The following three outcome measures will be used in the study: the Hospital Anxiety and Depression Scale (HADS), the Impact of Events Scale Revised, and the 5-level 5-dimension EuroQoL. All 3 measures will be completed at each of the 3 time points. The level of family support will also be collected at these time points via the Multidimensional Scale of Perceived Support [14]. Table 1 provides a brief description of each of the outcome measures. Participants in both groups will receive the 3 surveys by email 2 weeks post discharge from the hospital to complete the first data collection time point. At the following 2 data collection time points, the 3 surveys will be sent by via email to both groups. All participants will also be contacted by telephone to provide a prompt to complete the surveys at the data collection time points.

**Table 1 table1:** Summary of outcome measures and description.

Outcome measure		Number of items	Description
**Primary outcome**			
	Hospital Anxiety and Depression Scale	14 on a 4-point scale	Used to identify the incidence of anxiety and depression in patients with a range of diseases and medical conditions [15].
**Secondary outcomes**			
	Impact of Events Scale Revised	24 on a 5-point scale	Measure of subjective distress in response to a traumatic event [16]. It comprises 3 subscales that represent the major symptom clusters of posttraumatic stress disorder: intrusion, avoidance, and hyperarousal [17].
	5-level 5-dimension EuroQoL	5 on a 5-point scale and a visual analog scale	Measure changes to health-related quality of life over time or between or following interventions [18]. The 5 dimensions within the survey are mobility, self-care, usual activities, pain or discomfort, and anxiety or depression.
	Multidimensional Scale of Perceived Social Support	12 on a 7-point Likert scale	Measures perceptions of support from 3 sources: family, friends, and significant other [14].

For participants in the intervention group at time point 3, 12 months after discharge, an evaluation will be conducted via the website on the acceptability and usability of the website. The evaluation will be conducted through the Web portal and completed online. The evaluation tool will be a modified version of the Mobile App Rating Scale [19] and comprise questions on the acceptability and content of the Web-based recovery program. The website is multidimensional, including recovery resources and an internet-based community, and facilitates journaling. To further understand the contribution each makes to outcomes, we will analyze the website analytics to determine how frequently and for how long the participants interacted with the site and the individual components within it. Participants will also be asked to rate each component of the site in terms of usefulness and perceived impact on their recovery.

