### Statistical Analysis

Data will be reported in accordance with the Consolidated Standards of Reporting Trial. Data analysis will be conducted using SPSS version 24 (IBM) and Stata SE version 15 (StataCorp). The characteristics of participants in each arm of the study will be summarized using descriptive statistics. Analysis of characteristics to determine similarity between the arms will be conducted using chi-square tests for categorical data and independent *t* tests for continuous data.

Further analysis will include stratifying the APACHE III scores into categories to determine if there is a difference in the level of severity and outcomes. The 3 outcome measures (HADS, IES, and QoL) at follow-up will be analyzed as dependent variables using regression modeling. Covariates will include baseline outcome measures, study allocation (intervention or control), age, gender, length of ICU stay, APACHE III score, and level of family support. Analysis will be conducted on an intention-to-treat basis. A subanalysis of the intervention group based on those who engaged with the mobile website compared with those who did not will also be conducted. The characteristics of people who withdraw from the study will be compared with those who remain in the study. Missing data will be addressed using multiple imputation assuming variables are missing at random. The person who completes the data analysis will be blind to participant allocation status. Summary statistics of frequency of use, time spent using the site, most frequently used elements, and time spent on each screen will be reported.

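### The 12-month acceptability evaluation is run on the website it evaluates, so lapsed users are less likely to answer and ratings are likely to be too favourable (minor)

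*Protocol article*

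**What the plan says.** In the protocol article, the text after Table 1 (Data Collection and Measures) describes an extra assessment for the intervention arm at the third time point, 12 months after discharge: "an evaluation will be conducted via the website on the acceptability and usability of the website". The next sentence repeats the mode: "The evaluation will be conducted through the Web portal and completed online". The instrument is an adapted Mobile App Rating Scale. No email, postal or telephone alternative is named. The same paragraph says that website analytics will describe use of the site and its components, and that participants will rate each component. The sentence on component ratings states no route.

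Three other statements bear on who will answer:

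- Intervention: "The frequency of use of the website is at the discretion of the participants". No minimum use is set.
- Statistical Analysis: "A subanalysis of the intervention group based on those who engaged with the mobile website compared with those who did not will also be conducted". Non-engagement is thus foreseen.
- Data Collection and Measures, on the outcome questionnaires: "At the following 2 data collection time points, the 3 surveys will be sent by via email to both groups", and "All participants will also be contacted by telephone to provide a prompt to complete the surveys at the data collection time points".

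The Intervention section also provides weekly emails that flag days without participation and encourage return, and telephone or home-visit help for people who cannot use the site.

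**The concern.** The questionnaire sits inside the product that it measures. A participant who gave up on the site early must go back to it at 12 months to say that it was not acceptable. Someone who found it hard to use must use it to report that. The chance of answering therefore probably depends on the quantity being measured, and the respondents will lean towards continuing users.

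This is a stated choice of route. It is not a detail that the article has left to a fuller document.

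At stake is the process evaluation. The Abstract lists participants' evaluation of the site as something the trial will collect, and the Discussion says that the findings are to guide a bigger study. Ratings that describe mainly continuing users would be a poor guide to how the programme is received by everyone offered it. The reasons of people who stopped are also hard to recover once follow-up has closed.

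**Working it through.** **Step 1: the passages side by side.**

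| Item at 12 months | Who | Route stated | Prompt stated |
|---|---|---|---|
| HADS, IES-R, EQ-5D-5L | both arms | email | telephone |
| Acceptability and usability evaluation | intervention arm | the website | none specific to it |
| Component ratings | site users, by context | none stated | none stated |

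The outcome questionnaires do not depend on the portal. The evaluation does. The telephone prompt is worded for the surveys, which in context are the outcome questionnaires sent to both arms. Even if it also covers the evaluation, the participant must still return to the portal. Analytics measure use; they do not record acceptability or reasons for stopping. The multiple imputation in the Statistical Analysis section is not tied to this evaluation.

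**Step 2: the one figure available.** The plan states no figure for the evaluation. The only input is the arm size of 81 (Sample Size). With effect size 0.44, two-sided alpha 0.05 (sidedness is not stated) and 80% power, the normal approximation gives 2 × (1.960 + 0.842)² / 0.44² = 81.1 per arm. The plan's 81 is therefore reproduced to within rounding, and 81 is the largest possible number of evaluation respondents.

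**Step 3: the form of the bias.** Let q be the share who stopped using the site. Let r_u and r_s be the response rates of continuing and lapsed users, and a_u and a_s the proportions of each finding the site acceptable.

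- True value: (1 − q)a_u + q·a_s
- Observed value: [(1 − q)r_u·a_u + q·r_s·a_s] / [(1 − q)r_u + q·r_s]
- Observed minus true: q(1 − q)(r_u − r_s)(a_u − a_s) / [(1 − q)r_u + q·r_s]

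The bias is upward when lapsed users both answer less often and rate lower. It is zero if they answer as often as users, or rate the site equally well.

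**Step 4: illustration.** All inputs except 81 are assumptions: r_u = 0.9 and a_u = 0.8 throughout.

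| q | r_s | a_s | True | Observed | Difference | Respondents of 81 |
|---|---|---|---|---|---|---|
| 0.3 | 0.5 | 0.6 | 74.0% | 76.2% | +2.2 points | 63 |
| 0.5 | 0.5 | 0.4 | 60.0% | 65.7% | +5.7 points | 57 |
| 0.5 | 0.2 | 0.4 | 60.0% | 72.7% | +12.7 points | 45 |
| 0.7 | 0.2 | 0.4 | 52.0% | 66.3% | +14.3 points | 33 |

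For the third row: 0.5 × 0.5 × 0.7 × 0.4 / (0.45 + 0.10) = 0.07 / 0.55 = 0.127. Over q of 0.3–0.7, r_s of 0.2–0.5 and a_s of 0.4–0.6, the range is about +2 to +14 percentage points.

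**Step 5: worst case.** If no lapsed user answers (r_s = 0), the expression reduces to q(a_u − a_s). For a mean rating this is (1 − s) × g, where s is the share still using the site and g is the rating gap. With s assumed at 0.4–0.7 and g at 0.5–1.0 rating points, the bias runs from 0.3 × 0.5 = 0.15 to 0.6 × 1.0 = 0.60 points. If every continuing user also answers, there are 81 × 0.4 = 32 to 81 × 0.7 = 57 respondents.

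**The case against.** The case for leaving the plan alone has several parts.

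- **Prompts and support exist.** The evaluation falls at a time point when everyone is telephoned. Weekly emails encourage return, and help is offered to those who cannot use the site. An emailed link or a call may well lead people to the portal, and a condensed article need not say so. This stands in part: non-response may be smaller than feared. But the portal remains the only place named for answering.
- **Some restriction to users is inherent.** A person who never opened a component cannot rate it. This stands, and the fix allows for it.
- **Non-use is described elsewhere**, through the analytics and the comparison by engagement. This is true of use, but not of acceptability or reasons for stopping.
- **The email route is not free of selection.** Outcome questionnaires also have non-response, and the Control Group section calls the surveys postal, so the delivery mode is not fully settled. This stands: the email route merely avoids tying response to site use.
- **The stakes are low.** Acceptability is not in the stated objective and is not among the Table 1 outcomes. This stands and sets the severity.

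A reader might infer that acceptability is certain to be overstated, by 0.15–0.60 points, with only 32–57 people answering. The documents do not support that. They give no log-in rate, response rate or rating gap, and those figures are a worst case built wholly on assumptions. Nor do they say that the component ratings are collected only through the portal; that is an inference from the surrounding text.

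**Conclusion.** The point holds as a minor one. The plan fixes the evaluated website as the only named route for the acceptability and usability evaluation, while use is voluntary and non-engagement is expected. Lower response from lapsed users is therefore likely. Acceptability is likely to be overstated on the further assumption that those users rate the site lower, which is the expected pattern but is not shown in the documents.

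The size is unknown. The range of about 2 to 14 percentage points illustrates what plausible inputs would give and is not an estimate for this trial. The effect is confined to the process evaluation. The HADS comparison, the other outcome measures, the sample size and the cost utility analysis do not depend on it.

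**What to change.** Send the evaluation, including the component ratings, to all intervention participants by the 12-month email route already planned, cover it with the telephone prompt, and require no site log-in. Place it after the HADS, IES-R and EQ-5D-5L, so that rating the programme does not colour the outcome answers.

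Report the response rate over all participants allocated to the intervention. Report ratings by level of use taken from the website analytics, and limit each component's rating to those who used that component.

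The cost is one more survey link, a minor amendment and a slightly longer 12-month survey for the intervention arm. The ratings will probably be less favourable, but they will better represent the people offered the programme.
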